**Fig. 1 Fig1:**
[figure not shown]
**A** Schematic figure depicting the study design of the CONFIDENT-ENB trial. ENB, electromagnetic navigation bronchoscopy; CT, computed tomography; CONFIDENT-ENB, COmparison and synergistic evaluation of Needle aspiration and Forceps bIopsy for Diagnosing pulmonary lEsioNs wiTh Electromagnetic Navigation Bronchoscopy

This study is being conducted in accordance with the Declaration of Helsinki and all regulatory requirements. The protocol was approved by the institutional review board of Seoul National University Bundang Hospital (IRB no: B-2112-715-302), which is where patient enrollment and ENB procedures will be conducted. Informed consent will be obtained from all participants. The study is registered at ClinicalTrials.gov (NCT05110131). The results will be reported according to the Standards for Reporting Diagnostic Accuracy Studies (STARD) and the Consolidated Standards of Reporting Trials (CONSORT) statements.

### Randomization and baseline evaluation

After providing informed consent, the participants will be randomly allocated to a study group (needle precedence group or forceps precedence group). They will initially undergo ENB-guided biopsy with the modality of the allocated group (needle or forceps) followed by a biopsy with the other modality. Randomization will be performed by an independent statistician using a computer-generated list using SAS version 9.4 (SAS Institute, Cary, NC, USA). The attending physicians have no role in the assignment process and will be blinded to the allocation. The physicians who will perform the ENB procedure are also blinded to the allocation until the preparation of ENB on the day of the procedure.

The enrolled participants will be evaluated for demographic, clinical, and radiological characteristics at baseline (within 30 days of the procedure) and on the procedure day. The complete list of baseline demographic data and lesion characteristics evaluated with the pre-procedural chest CT is listed in Table 1. Additionally, the pre-procedural probability of malignancy of the lesion will be evaluated for each lesion using the Brock model [3].

**Table 1 Tab1:** Basic characteristics of the participants

Demographics
Age (years)
Sex
Race
Smoking status
Pack-years smoked
Family history of lung cancer
Clinical characteristics
Performance status
History of lung cancer diagnosis
History of malignancies other than lung cancer
Prior invasive lung procedures and surgery
Radiological characteristics
Lesion location (lung lobe)
Lesion type (solidity)
Lesion size
Size of solid proportion
Lesion shape (speculated margin, cavity formation, bubble lucency)
Pre-procedural probability of malignancy
Distance from lesion to pleura
Emphysema surrounding lesion
Interstitial fibrosis surrounding lesion
Bronchiectasis surrounding lesion
Presence and type of bronchus sign
Combined lymphadenopathy
Positivity on positron emission tomography (if applicable)
Procedural characteristics
Preceded modality
Capability to navigate and localize the lesion
Number of biopsy attempts (for each modality)
Acquisition of a core tissue available for histologic examination (for each modality)
Procedure duration
Sequential linear EBUS for nodal staging
Total dose of sedatives used

*EBUS* Endobronchial ultrasound

### Procedures

ENB procedures will be performed using the Spin Thoracic Navigation System (SYS-4230 K; Veran Medical, St. Louis, MO, USA) by one of nine pulmonologists ([name], [name], [name], [name], [name], [name], [name], [name], and [name], each having at least 3 years of experience with bronchoscopic procedures). On the day of the procedure, the patients will undergo inspiration/expiration chest CT before the procedure for the correlation with the navigation platforms and reconstruct virtual airway routes. The ENB procedures will be performed according to the product instructions under moderate sedation with intravenous administration of 2–3 mg midazolam and 25–50 µg fentanyl at the procedure onset. The performing physician may administer additional midazolam or fentanyl during the procedure to achieve adequate sedation. A bronchoscope with an outer diameter of 5.9 mm (BF-1TQ290), 4.9 mm (BF-260), or 4.0 mm (BF-P260F) (all Olympus Corporation, Tokyo, Japan) is used for ENB procedures. According to the allocated group, ENB-guided biopsy will be first attempted at least three times with a 22 G or 21 G aspirating needle or forceps followed by the same procedure with the other modality with at least three attempts. There are no protocol-specific restrictions on the maximum attempts and the number of attempts is subjective to the performing physician’s discretion. Successful localization and approach to the lesion, number of biopsy attempts, total procedure time, and successful acquisition of a core tissue for histological examination for each modality will be recorded.

Following biopsy using both the methods, bronchoalveolar lavage (BAL) will be performed by placing the bronchoscope into the lung segment in which the biopsy was performed. After wedging, 30 mL sterile normal saline will be instilled followed by the recovery of the specimen in a sterile container. If the retrieved lavage fluid is insufficient for cytological examination, the performing physician may additionally perform BAL. All ENB procedures will be controlled and will not include any other complementary imaging techniques, such as radial endobronchial ultrasonography (EBUS), fluoroscopy, and rapid on-site examination (ROSE). Lymph node staging using linear EBUS may be performed after the ENB procedure at the discretion of the attending physician.

Using the ENB procedure, biopsy samples from the needle and forceps biopsies, cytology samples from needle aspiration, and cytology samples from BAL are expected from each participant. All samples will be evaluated by experienced pulmonary pathologists who are blinded to the results of other sampling methods and clinical information of the patient.

### Diagnosis and follow-up

All cases with histopathologically confirmed malignancy based on either ENB-guided needle biopsy or cytology, forceps biopsy, or BAL cytology are determined as positive for malignancy. The histopathological results of the biopsied samples that reveal no malignancy or indeterminate findings are initially considered negative. In such cases, the attending physician will conduct follow-up for at least 12 months and make decisions to perform additional invasive procedures to determine the true diagnosis (gold standard) accordingly. The final diagnosis will be determined at 12 months from the procedure. The following cases will be defined as false negatives: (1) malignancy based on a repeat biopsy (e.g., surgical biopsy, CT-guided TTNA, and bronchoscopic); (2) growth of the lesion observed on serial follow-up CT within 12 months; (3) treated as lung cancer without pathological confirmation; and (4) lung cancer diagnosed at other sites (including non-index lesions or lymph nodes diagnosed using linear EBUS during or after the index procedure) within 6 months. The following cases will be defined as true negatives: (1) subsequent diagnostic procedures confirm a non-malignant diagnosis; (2) an initial non-malignant lesion resolved without cancer treatment (e.g., improved proven infectious disease or transient inflammation); or (3) no lesion progression observed on radiographic follow-up for 12 months.

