### Objectives and endpoints

The primary endpoint is the diagnostic performance of ENB-guided needle biopsy and forceps biopsy and the yield achieved by combining the modalities based on the 12-month clinical follow-up. Secondary endpoints include a comparison of successful approach to the lesion, duration of sampling time, number of attempts, and successful acquisition of core tissue between the needle and forceps biopsy techniques. Additionally, all adverse events related to the ENB procedure or sedatives will be captured and classified according to the Common Terminology Criteria for Adverse Events (CTCAE) scale, version 5.0 [26]. Pneumothorax will be confirmed using chest X-rays performed post-procedurally and the day after the procedure. All participants will be followed up at 2 weeks post-procedure to evaluate the presence of delayed complications. The detailed definitions of outcomes are presented in Table 2.

**Table 2 Tab2:** Definitions and overview of study endpoints

Primary endpoint: diagnostic values
- Primary endpoints will be calculated separately for needle aspiration, forceps biopsy, and the combination of the two. For initially negative results, the final diagnosis will be confirmed based on the 12 months of clinical follow-up
- Diagnostic accuracy:
Proportion of subjects in whom the ENB-guided biopsy yielded a definite diagnosis = (malignant and benign diagnosis by modality)/(biopsied lung lesions)
- Sensitivity:
= (Malignancy confirmed by modality)/(Number of malignancies confirmed at 12-month follow-up)
- Specificity:
= (Benign confirmed by modality)/(Number of benign lesions confirmed at 12-month follow-up)
- Positive predictive value:
= (True malignant lesions)/(Number of malignant lesions by modality)
- Negative predictive value:
= (True benign lesions)/(Number of benign lesions by modality)

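### The protocol gives no rule by which a malignant index result can be found false, so PPV is fixed at 100% and one tool's false positive is scored as the other tool's miss

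*Protocol article*

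**What the plan says.** **Protocol article, Diagnosis and follow-up.** A histopathologically confirmed malignancy on needle biopsy or cytology, forceps biopsy "or BAL cytology are determined as positive for malignancy". The text then turns to samples that are non-malignant or indeterminate: "In such cases, the attending physician will conduct follow-up for at least 12 months", with further invasive procedures as needed to reach the true diagnosis. Two outcome classes receive criteria: "The following cases will be defined as false negatives" (four criteria) and "The following cases will be defined as true negatives" (three). No criterion for a false positive appears anywhere.

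**Table 2 (Objectives and endpoints).** The same limit is stated: "For initially negative results, the final diagnosis will be confirmed based on the 12 months of clinical follow-up". Three formulas matter here:
- diagnostic accuracy (yield): "malignant and benign diagnosis by modality)/(biopsied lung lesions"
- sensitivity: "Malignancy confirmed by modality)/(Number of malignancies confirmed at 12-month follow-up"
- PPV: "True malignant lesions)/(Number of malignant lesions by modality"

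Specificity is listed alongside them. All are calculated for needle, for forceps and for the two combined; BAL is not part of the combination.

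**General statements.** The Abstract says that all participants are followed for up to 12 months to settle the final diagnosis, and Diagnosis and follow-up places that diagnosis at 12 months. Neither says when a malignant index result would be reversed.

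**The concern.** The reference standard is spelled out in one direction only. For positives, the index specimens serve as their own reference. That conflicts with Table 2, where PPV and specificity make sense only if a malignant call can be wrong.

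It also affects the comparison the trial was built for. The sample size rests on the gain of the combination over a single modality, and the trial also aims to assess discordance between the tools. Lesions positive on one tool only supply both. If one of these is a false positive, the written rule places it in the sensitivity denominator, credits the erring tool and the combination, and charges a missed cancer to the tool that was right. An analyst who follows the text has no rule under which to reclassify a lesion that is later resected and contains no cancer.

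**Working it through.** **The plan's own figure.** Under independence, discordance is 0.67 × 0.18 + 0.82 × 0.33 = 0.391, stated as 39%. For McNemar's test with difference d = 0.15, discordance 0.39, two-sided 0.05 and 80% power:

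n = [1.960 × √0.39 + 0.842 × √(0.39 − 0.15²)]² / 0.15² = 133.7, so 134; 134 / 0.95 = 141.05, so 142.

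The stated 142 is reproduced, and nothing below changes it.

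**Assumptions for the size of the effect.** The protocol gives no malignancy split and no false-positive rate. I take 107 malignant and 35 benign lesions out of 142. Each tool truly finds 72 malignancies (67.3%) and the combination finds 88 (82.2%). The protocol's 67% and 82% are yields; using them as sensitivities is only illustrative. The combination is taken as positive when either tool is, which is the natural reading but is not stated.

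**Sensitivity as scored.** With k needle-only false positives, needle = (72 + k)/(107 + k), forceps = 72/(107 + k), and combination = (88 + k)/(107 + k).

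| Case | Needle | Forceps | Combination | Needle − forceps |
|---|---|---|---|---|
| No false positive | 72/107 = 67.3% | 72/107 = 67.3% | 88/107 = 82.2% | 0 |
| 1 needle-only | 73/108 = 67.6% | 72/108 = 66.7% | 89/108 = 82.4% | 0.9 points |
| 3 needle-only | 75/110 = 68.2% | 72/110 = 65.5% | 91/110 = 82.7% | 2.7 points |
| 1 BAL-only | 72/108 = 66.7% | 72/108 = 66.7% | 88/108 = 81.5% | 0 |

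The gap is k/(107 + k). With only 80 malignancies it would be 1/81 = 1.2 points for one case and 3/83 = 3.6 points for three.

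**Gain of the combination in sensitivity at k = 3.** Over forceps it rises from 16/107 = 15.0% to 19/110 = 17.3%. Over needle, the erring tool, it falls from 15.0% to 16/110 = 14.5%.

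**Yield.** One needle-only false positive adds 1/142 = 0.7 points to the combination's yield over forceps (1/134 = 0.75 on the evaluable number). This holds only if forceps gave no definite diagnosis. The yield formula also counts benign diagnoses, so a definite benign forceps result is already a success.

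**PPV and specificity at k = 3.** Needle PPV against the truth is 72/75 = 96.0%; as scored it is 75/75 = 100%. If needle called the other 32 benign lesions benign, its true specificity is 32/35 = 91.4%. As scored, the three lesions leave the benign denominator and it becomes 32/32 = 100%.

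**The case against.** The strongest reply is that the protocol never says a positive is irrevocable. A reader might infer that nothing found later can overturn one, but this comes from the missing criterion and not from a stated prohibition. All participants are followed, the final diagnosis is dated to 12 months in general terms, the sensitivity denominator refers to malignancies confirmed at 12 months, and the PPV numerator presupposes a truth separate from the call. This stands as evidence that a separate truth status is intended. It does not supply a way to reach one for an index-positive lesion. Condensation explains this poorly, because the article sets out seven criteria for negatives and twice confines the 12-month determination to initially negative results.

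A reader might also infer that the rule always favours the combination. The documents do not support that. The gain over the erring tool does not rise, a false positive shared by both tools adds no gain over either, and a definite benign result from the other tool removes the yield effect. A BAL-only false positive lowers the combination's sensitivity.

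Finally, the threshold for a positive is conservative: malignancy must be histopathologically confirmed, indeterminate findings count as negative, and pathologists are blinded to the other samples and to clinical information. False positives may therefore be rare. That limits the size of the problem but does not remove the conflict with PPV and specificity.

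**Conclusion.** The point holds in this limited form. Under the written rules a malignant call by any one specimen is accepted as true. PPV is therefore 100% by construction, and specificity cannot be lowered by a false malignant call. Both follow from the text and need no assumed rate.

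The effect on the tool comparison depends on an unknown count. For 0 to 3 one-tool false positives (0 to 9% of 35 benign lesions, an assumption), the spurious sensitivity gap is 0 to 2.7 points with 107 malignancies. The spurious yield gain over the other tool is at most 3/142 = 2.1 points. Against a planned 15-point difference this is probably small, and zero is within the range. The documents do not support a conclusion that the trial's main result would be unreliable, and the sample size is unaffected. The rule is nevertheless worth correcting, because it governs primary measures and any error of this kind would go unseen in the results.

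**What to change.** Add to Diagnosis and follow-up wording such as:

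> An index-positive lesion is finally classed as benign, and as a false positive for each modality that called it malignant, if (a) surgical resection of the index lesion without prior cancer treatment shows no malignancy, or (b) a specific benign diagnosis is later made and the lesion resolves by 12 months without cancer treatment. A repeat biopsy that is merely non-diagnostic or non-malignant does not overturn a positive. Positives without later tissue or such follow-up are accepted as true.

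The criterion is deliberately narrow. A non-malignant repeat biopsy may be a sampling miss, and tissue taken after cancer treatment may be clear because of the treatment. Either could relabel true positives as false.

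Use this final diagnosis in every Table 2 measure and in the paired comparisons, and report the number of overturned positives for needle, forceps and the combination, and for BAL-only calls.

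**Cost.** Protocol or SAP wording, plus review of later pathology and follow-up records that already exist. No procedure is added, and the 142 and clinical management are unchanged. The downside is that verification of positives stays partial, since it depends on who has later tissue or documented resolution. Yield, sensitivity or PPV may also become slightly less favourable.

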**Methods:**

The trial will recruit 142 participants with lung lesions suspected of malignancy who are eligible for an elective ENB procedure under moderate sedation. Participants will undergo ENB-guided needle aspiration and forceps biopsy in a randomized order without the use of any complementary techniques. All participants will be followed up subsequently for up to 12 months to conclude the final diagnosis of the biopsied lesions. Primary outcomes include the diagnostic yield and sensitivity of each biopsy modality and the diagnostic yield of the combined modalities.

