## Methods/design

### Study design and subject eligibility

We designed a prospective, randomized trial to evaluate the synergistic diagnostic yield of ENB-guided needle aspiration biopsy and ENB-guided forceps biopsy by performing biopsy with both the devices in a random order (Fig. 1). This study aims to enroll approximately 142 participants from a tertiary center in South Korea by 11 pulmonary physicians. All consecutive patients over the age of 18 years who are candidates for an elective ENB procedure for histopathological evaluation of peripheral lung lesions suspected of malignancy but predicted to be unreachable with conventional bronchoscopy alone are eligible for enrollment. The exclusion criteria are: (1) patients unable or unwilling to provide informed consent or comply with the follow-up schedule; (2) patients who have participated in an investigational drug or device research study within 90 days of enrollment, with possible interference with this study; (3) patients with a history of intolerance to moderate sedation or allergies to any of the sedatives planned to use, those with comorbidities contraindicating the bronchoscopy procedure, those on mechanical ventilation or who underwent a tracheostomy, or those who are pregnant; (4) patients with multiple lesions that need to be sampled with ENB-guidance; and (5) patients who were initially planned to undergo ENB but successfully underwent biopsy from a visible endobronchial tumor lesion, which precluded the need for electromagnetic navigation, or those who failed to perform ENB-guided biopsy with both modalities.

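### The fourth false-negative criterion can turn a benign index lesion into a missed cancer, and the plan does not say which list prevails when a lesion meets both

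*Protocol article*

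**What the plan says.** The Abstract (Methods) states that participants are "followed up subsequently for up to 12 months to conclude the final diagnosis of the biopsied lesions". In Table 2 (Objectives and endpoints) the accuracy formula is "malignant and benign diagnosis by modality)/(biopsied lung lesions". Specificity and the predictive values there are also defined on lesions, and sensitivity is defined on malignancies confirmed at 12 months.

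The Diagnosis and follow-up section sets the reference standard for cases whose initial samples show no malignancy. It lists four ways to be a false negative. The second looks at the lesion itself: "growth of the lesion observed on serial follow-up CT within 12 months". The fourth looks elsewhere: "lung cancer diagnosed at other sites (including non-index lesions or lymph nodes diagnosed using linear EBUS during or after the index procedure) within 6 months".

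Three entries make up the true-negative list: "subsequent diagnostic procedures confirm a non-malignant diagnosis", "an initial non-malignant lesion resolved without cancer treatment" and "no lesion progression observed on radiographic follow-up for 12 months". The section does not say what happens when a case satisfies an entry on each list.

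On eligibility, exclusion 4 removes only "patients with multiple lesions that need to be sampled with ENB-guidance". Table 1 records a history of lung cancer as a baseline item, and it is not an exclusion.

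**The concern.** The fourth criterion takes the label of the index lesion from a different lesion. It does not require the index lesion to be malignant, unresolved or part of the cancer found elsewhere. A patient with one lesion targeted by electromagnetic navigation bronchoscopy (ENB) and a second lesion sampled by another route is eligible. Suppose the ENB lesion is a granuloma and the second lesion proves to be lung cancer at month 4. Both tools were right about the lesion they sampled, yet the fourth criterion makes the case a false negative. If the granuloma is later proven, resolves or stays stable, the same case is also a true negative.

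At stake are the absolute values of sensitivity and NPV, which Table 2 lists among the primary measures, and the count of benign lesions on which specificity rests.

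**Working it through.** **The plan's own figure.** The section on the statistical plan and sample size gives yields of 67% and 82%, 39% discordance, two-sided 0.05, 80% power and 5% dropout. The McNemar formula is n = [z(0.975)·√pd + z(0.80)·√(pd − d²)]² / d². With pd = 0.39 and d = 0.15:

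- [1.960·√0.39 + 0.842·√0.3675]² / 0.0225 gives n = 134 after rounding up.
- 134 / 0.95 gives 142 after rounding up, as stated.

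No input to this calculation depends on how a negative case is later labelled.

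**The overlap.** Take a non-index lung cancer found at month 4 after an initially negative index biopsy.

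- Index lesion later proven non-malignant: fourth false-negative criterion and first true-negative criterion.
- Index lesion resolves untreated: fourth false-negative criterion and second true-negative criterion.
- Index lesion stable for 12 months: fourth false-negative criterion and third true-negative criterion.

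**Effect of k relabelled lesions.** Evaluable lesions: 142 × 0.95 ≈ 135. Assumptions not in the document: 70% of lesions malignant (94 malignant, 41 benign); the planned yields borrowed as sensitivities (77 of 94 for the combination, 63 of 94 for a single tool); no false positives; every result without malignancy counted as benign by modality. Then

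- sensitivity = TP / (94 + k)
- NPV = (41 − k) / (41 + 94 − TP), with denominator 58 for the combination and 72 for a single tool.

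| k | Combination sensitivity | Combination NPV | Single-tool sensitivity | Single-tool NPV |
|---|---|---|---|---|
| 0 | 77/94 = 81.9% | 41/58 = 70.7% | 63/94 = 67.0% | 41/72 = 56.9% |
| 1 | 77/95 = 81.1% | 40/58 = 69.0% | 63/95 = 66.3% | 40/72 = 55.6% |
| 3 | 77/97 = 79.4% | 38/58 = 65.5% | 63/97 = 64.9% | 38/72 = 52.8% |
| 5 | 77/99 = 77.8% | 36/58 = 62.1% | 63/99 = 63.6% | 36/72 = 50.0% |

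The benign denominator for specificity falls from 41 to 41 − k.

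**Range.** With 60% to 80% malignant and k from 1 to 5:

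- The sensitivity loss runs from 0.6 points (72/108 to 72/109) to 4.7 points (66/81 to 66/86).
- The NPV loss runs from 1.2 points (54/81 to 53/81) to 10.9 points (27/46 to 22/46).

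**The paired comparison.** The criterion reaches only cases without malignancy on needle, forceps and lavage. For malignancy these are concordant pairs, so in the 70% example the 77 − 63 = 14 discordant lesions stay the same for any k. The sensitivity gap moves only from 14/94 = 14.9 points to 14/97 = 14.4 points at k = 3. Some effect on yield is possible where one tool gave a definite benign result and the other did not.

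**The case against.** The criterion has a rationale. Enrolled lesions are suspected of malignancy. Once cancer is proven elsewhere, the index lesion may never be sampled again, and treatment can obscure later imaging. Counting such a case as missed avoids flattering the tools. This carries most weight for lymph nodes, where a positive node may well point to the index lesion as the primary, so the nodal part is defensible. It does not justify overriding direct evidence that the index lesion is benign.

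A condensed article may also leave adjudication detail to the full protocol, which is not shown. An unstated tie-break could exist there. But the two lists as printed conflict, and the conflict lies in the definition of the reference standard itself.

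A reader might infer three stronger things that the text does not support:

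- *The whole reference standard is at patient level.* It is mixed. The second false-negative criterion and the true-negative criteria concern the lesion.
- *Benign index lesions will be counted as missed cancers whenever cancer is found elsewhere.* They can be, because the true-negative list may apply to the same case.
- *A second cancer after month 6 automatically leaves the index lesion benign, so the window should be 12 months.* The other three false-negative criteria still operate after month 6, and a true-negative criterion must be met. The shorter window can be read as limiting the rule to cancer plausibly present at the procedure, and lengthening it would admit later, possibly unrelated cancers.

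**Conclusion.** The concern holds as a contradiction between two lists in the primary reference standard, together with one criterion that can misclassify the lesion under study. It is confined to cancers in non-index lesions.

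The direction is clear: sensitivity and NPV go down for all three strategies. The size is not known, because the document gives neither the proportion of malignant lesions nor the number of affected patients. With one case the combination loses less than a point of sensitivity. With five, under the 70% assumption, it loses about 4 points of sensitivity and nearly 9 of NPV.

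It would be wrong to conclude that the needle-forceps comparison or the sample size fails. Both are largely untouched. This is a correction worth making, but it does not undermine the design.

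**What to change.** Reconcile the two lists in the Diagnosis and follow-up section:

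- State that evidence on the index lesion itself takes precedence over the fourth false-negative criterion. That evidence is benign pathology, resolution without cancer treatment, or 12-month stability without cancer treatment. The last condition matters because treatment of the other cancer could keep a malignant index lesion stable.
- Apply the non-index part only when the index lesion is judged part of the same cancer, by an assessor blinded to which tool returned which result.
- Keep the nodal part where no other primary explains the node, and keep the 6-month window.
- Class the remaining cases as indeterminate. Report sensitivity, specificity and NPV with them counted as malignant and as benign, and also under the current wording.

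This uses follow-up data already planned and needs no new visits or procedures. The costs are a few indeterminate lesions, an added judgement step, and a reference-standard rule clarified after enrolment began in December 2021. The change should therefore be documented before the 12-month final diagnoses are analysed.

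### True-negative rule 3 has no cancer-treatment condition, so a missed non-lung malignancy held stable by treatment is scored as benign

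*Protocol article*

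**What the plan says.** The Diagnosis and follow-up section of the protocol article calls a case positive if needle biopsy or cytology, forceps biopsy or lavage cytology shows malignancy. All other cases are initially negative and are settled at 12 months by two numbered lists.

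False negatives:

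1. "malignancy based on a repeat biopsy"
2. "growth of the lesion observed on serial follow-up CT within 12 months"
3. "treated as lung cancer without pathological confirmation"
4. "lung cancer diagnosed at other sites", limited to 6 months

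True negatives:

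1. a later procedure confirms a non-malignant diagnosis
2. "an initial non-malignant lesion resolved without cancer treatment"
3. "no lesion progression observed on radiographic follow-up for 12 months"

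In Table 2 (Objectives and endpoints) the sensitivity denominator is "Number of malignancies confirmed at 12-month follow-up", which is not restricted to lung cancer. NPV is listed there under the primary endpoint, and the Abstract names sensitivity among the primary outcomes. None of the exclusion criteria concerns previous or concurrent cancer, and Table 1 records "History of malignancies other than lung cancer" at baseline.

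**The concern.** True-negative rule 2 accepts resolution only when no cancer treatment was given, so the plan recognises that treatment can imitate a benign course. Rule 3 drops that condition. A lesion that shrinks or disappears under cancer treatment has also not progressed, so rule 3 admits what rule 2 refuses.

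The false-negative list does not close the gap for cancers other than lung cancer. Its rules on treatment and on diagnosis elsewhere are limited to lung cancer, although the target condition is malignancy in general and patients with other cancers are eligible.

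Each case mislabelled in this way leaves the sensitivity denominator and enters the NPV numerator. Both measures then look better than they are for needle, forceps and combination, and the benign group used for specificity contains a cancer.

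**Working it through.** **The plan's own figure.** The only computed figure is the sample size. For paired proportions, n = (z₁√p_d + z₂√(p_d − d²))² / d². With d = 0.82 − 0.67 = 0.15, p_d = 0.39, two-sided alpha 0.05 and power 80%, n = 133.7, so 134. Then 134 / 0.95 = 141.1, so 142. The stated 142 reproduces, and this point does not touch it.

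**Rule walk.** Three kinds of missed cancer, each negative on both tools and lavage, not re-biopsied, and stable or smaller at 12 months under treatment:

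| Rule | A. Metastasis of a known non-lung cancer, systemic treatment given | B. Lung cancer, treated empirically | C. Lung cancer proven at another site in months 7–12, then treated |
|---|---|---|---|
| False negative 1 (repeat biopsy) | no | no | no |
| False negative 2 (growth) | no | no | no, if no growth before treatment |
| False negative 3 (treated as lung cancer) | no | **yes** | depends on the reading |
| False negative 4 (lung cancer elsewhere, 6 months) | no | no | no, window closed |
| True negative 3 (no progression) | **yes** | **yes** | **yes** |

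- A meets only the true-negative rule and is scored benign.
- B meets one rule from each list, and no precedence is stated.
- C turns on the missing pathological confirmation in false-negative rule 3. If this means confirmation of the index lesion, the rule applies and C is an overlap like B. If it means confirmation anywhere, the rule fails and C is scored benign like A.

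**Size.** The documents give no prevalence of malignancy and no count of affected cases, so these are assumptions:

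- Evaluable lesions: 142 × 0.95 = 134.9, taken as 135.
- Malignant: 70%, 135 × 0.70 = 94.5, taken as 94. Benign: 41.
- Combined sensitivity: 82%, borrowed from the diagnostic yield in the sample-size section. 0.82 × 94 = 77.1, so 77 found and 17 missed.

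If k missed cancers are scored benign, sensitivity = 77 / (94 − k) and NPV = (41 + k) / (41 + 17).

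| k | Combined sensitivity | Combined NPV |
|---|---|---|
| 0 | 77/94 = 81.9% | 41/58 = 70.7% |
| 1 | 77/93 = 82.8% | 42/58 = 72.4% |
| 3 | 77/91 = 84.6% | 44/58 = 75.9% |

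A single tool at the plan's 67% finds 63 of 94 and misses 31. One case moves its sensitivity from 63/94 = 67.0% to 63/93 = 67.7%, and its NPV from 41/72 = 56.9% to 42/72 = 58.3%.

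Effect of one case on the combination at other assumed prevalences, still with 135 lesions and about 82% sensitivity:

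- 80% malignant (108, with 89 found, 19 missed, 27 benign): sensitivity 89/108 = 82.4% to 89/107 = 83.2%; NPV 27/46 = 58.7% to 28/46 = 60.9%.
- 90% malignant (121, with 99 found, 22 missed, 14 benign): sensitivity 99/121 = 81.8% to 99/120 = 82.5%; NPV 14/36 = 38.9% to 15/36 = 41.7%.

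One case is thus worth about 0.7 to 0.9 points of combined sensitivity and 1.7 to 2.8 points of NPV.

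**Paired comparison.** These cases are negative on needle, forceps and combination alike. They are concordant under either label, so the discordant counts in McNemar's test do not change.

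**The case against.** The strongest objection is that the usual missed case in this trial is lung cancer, and the plan largely covers it. Empirical treatment triggers false-negative rule 3, and proof elsewhere within 6 months triggers rule 4. A reader might infer that any missed cancer kept stable by treatment is scored as a true negative. The documents do not support that: for empirically treated lung cancer the defect is two rules with no stated order.

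The months 7–12 route is also not established. It fails if the missing confirmation refers to the index lesion, which is a natural reading, and it needs a lesion that did not grow before treatment. The 6-month limit may be deliberate, since a longer window could count unrelated new cancers as misses.

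The metastasis route is narrow: a non-lung malignancy, missed by both tools and lavage, not re-biopsied, treated, and without growth. The attending physician may order further invasive procedures, and false-negative rule 1 covers any malignancy found that way. Because this is discretionary, it narrows the gap but does not close it.

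A reader might also infer that the main comparison is biased or that several points of sensitivity are at stake. The first does not follow, because the cases are concordant. The second has no support: 3 of 17 would already mean that 18% of all misses take this route, and nothing in the documents indicates such a share.

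What stands is the metastasis route and the missing precedence.

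**Conclusion.** The point holds in a limited form. As written, the reference standard gives a wrong label to a missed, unre-biopsied non-lung malignancy held stable or shrunk by systemic treatment. It gives two labels to an empirically treated, stable lung cancer. For lung cancer proven elsewhere in months 7–12 the wording is ambiguous, and no more can be claimed.

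The consequence is upward bias in absolute sensitivity and NPV and a contaminated benign denominator. The powered single-versus-combined comparison stands. The per-case size above rests on assumed prevalence and on a yield used as sensitivity. The number of cases is unknown and probably small. The wording should still be corrected, because the affected measures are primary and the error is in a stated definition.

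**What to change.** In Diagnosis and follow-up, before the 12-month classification is made:

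- Add to true-negative rule 3 the condition *without cancer treatment that could have affected the lesion*.
- Widen false-negative rule 3 to *treated as malignancy (primary or metastatic) without pathological confirmation of the index lesion*. This also settles the months 7–12 ambiguity when the index lesion is treated as malignant, with no need to lengthen the window in rule 4.
- State that false-negative rules take precedence over true-negative rules.
- Class as indeterminate a lesion that is stable or smaller under cancer treatment, has no pathology and was not treated as malignant. Report sensitivity and NPV with such lesions counted both ways.

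These changes affect outcome classification only, not patient care. The cost is that cancer treatment during follow-up must be recorded for every initially negative case. True-negative rule 2 and false-negative rule 3 already need part of this, but Table 1 covers baseline history only. A few truly benign lesions will become indeterminate in an already small benign group, and sensitivity and NPV may come out slightly lower. Limiting the condition to treatment that could have affected the lesion keeps that loss small.
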